#### Comorbidity with other psychiatric disorders

The German version of the Structural Clinical Interview for DSM-IV (SCID-I and II-Interview) [76, 77] records comorbid psychiatric diagnoses according to DSM-IV criteria and will be administered at baseline, end of treatment and at one and two-year follow-ups. Previous studies demonstrated adequate to good interrater reliability. Diagnostic interviews (BPDSI-IV and SCID) are based on the DSM-IV classification system [78] because the DSM-5 [1] was not available when the study was planned and diagnostic instruments for the DSM-5 were not available at the beginning of the study.

#### Other BPD measures

The BPD checklist is a self-report scale that assesses the subjective burden that is caused by BPD manifestations. Research has established that this measure is suitable for use as a treatment outcome [79]. The Questionnaire of Thoughts and Feelings (QTF) assesses feelings, strategic cognitions, and assumptions that are characteristic of BPD. The QTF has shown excellent internal consistency (Cronbach’s alpha 0.91), high one-week test-retest reliability (*r* = 0.81) and high sensitivity to change over time in a sample of BPD patients during crisis intervention and eight months later [80, 81].

#### Dissociation

Dissociation is measured with the Dissociation Tension Scale (DSS), which is a self-report instrument that evaluates psychological, and somatoform dissociative features as well as the aversive inner tension that occurred in the past seven days. The DSS has high internal consistency (Cronbach’s alpha = 0.92), good validity, and sensitivity to change [82].

#### General psychopathology

The Brief Symptom Inventory (BSI) is an inventory of general psychiatric symptoms. The BSI was developed as a short version of the 90-item Symptom-Check-List (SCL-90-R), and has good psychometric properties [83]. The severity of depressive symptoms is measured with the self-rated 16-item version of the Quick Inventory of Depressive Symptomatology (QIDS-SR16), which has highly acceptable psychometric properties and is a treatment sensitive measure [84].

Difficulties in emotion regulation are assessed with the Difficulties in Emotion Regulation Scale (DERS), which has high internal consistency, good test-retest reliability, and adequate construct and predictive validity [85].

#### Rejection Sensitivity

The expectation of social rejection in close relationships is measured with the German version of the Rejection Sensitivity Questionnaire (RSQ) [86]. This questionnaire asks patients about 20 hypothetical situations in which they might experience rejections for their request for advice, help or companionship. Each situation is associated with two questions about (a) the level of concern and anxiety in this situation and (b) their expectation of the reaction (rejection or acceptance). The German version of the RSQ has high internal consistency (Cronbach’s alpha = 0.94) and test-retest-reliability (Pearson correlation after 2 weeks r_tt_ = .90). Rejection sensitivity was highly correlated with borderline-specific cognitions [86].

#### Therapeutic alliance

The Working Alliance Inventory (WAI) is one of the most commonly used and extensively validated measures of therapeutic alliance [87]. Many studies have shown that the quality of the working alliance predicts therapeutic success [88]. This was also demonstrated in the first outcome study on ST. This study found that ST had higher ratings on the WAI for both patients and therapists compared to TFP. Negative ratings were predictive of drop-out, while positive ratings at the beginning of treatment predicted subsequent clinical improvements [89]. In the PRO*BPD-study, we record the WAI from patients after the third session and at every subsequent assessment point. A group version of the WAI assesses the working alliance between the patient and other group members as well as between patient and group therapist. It is administered after the third group session and at every subsequent assessment point.

#### Method-specific measures

The Dialectical Behavior Therapy Ways of Coping Checklist (DBT-WCCL) [90], the Schema-Mode-Inventory (SMI) [91] and the Young Schema Questionnaire (YSQ) [92] serve as method-specific measures. The DBT-WCCL is a psychometrically sound measure that assesses DBT skill use [90]. Skill use mediates the decrease in suicide attempts and depression as well as the increase in control of anger in BPD patients who are treated with DBT [93]. The SMI is a self-report instrument that assesses the extent to which each of the 16 modes is present at the time of the assessment. It has an acceptable internal and high consistency for its subscales (Cronbach’s alpha ranges from 0.79 to 0.96), adequate test-retest reliability and moderate construct validity [91, 94]. The YSQ measures the presence or absence of 16 core maladaptive schemas at the time of the assessment. It has an adequate internal consistency and good reliability [95].

#### Treatment retention

If a patient drops out of treatment, the therapist completes a questionnaire that assesses the reasons for dropout. If the patient agrees, he is invited for the additional assessments that were scheduled at the beginning of treatment. Patients can stop the treatment program before 1.5 years and are viewed as an ‘early success’ if their BPDSI score is less than 15 and the therapist team agrees that the patient should stop the program. Patients may also be ‘pushed out’ of the treatment program e.g. if they continue to miss treatment sessions after interventions to increase attendance failed, if they deal with drugs or endanger the safety of other participants or therapists in other ways. We decided not to define explicit rules for a patient to be ‘pushed out’ of both conditions. It should be noted, that this is a difference from the standard DBT protocol, which states that missing four consecutive weeks of group sessions or four consecutive individual sessions will lead to treatment termination [22]. In the PRO*BPD trial a ‘push out’ is always decided by the therapist team and the local supervisors and is consistent with the respective treatment manual besides the above-mentioned divergence. In general, DBT has stricter rules about attendance, doing homework, the structure and content of therapy sessions (e.g., commitment to work according to the DBT hierarchy) compared to ST.

#### Statistical analyses of the clinical effectiveness study

Data analyses will be performed based on the intention-to-treat principle (including all patients regardless of whether they drop out from treatment or not) and will use all available data. Data for the primary and most secondary outcome measures will be analyzed with multilevel analysis to compare DBT to ST (mixed regression models for repeated measures). Time will be modelled according to the best model fit, e.g., a linear, logarithmic, or a segmented development of scores over time. The treatment by time interaction will be the primary test for treatment differences. We will use a piece-wise regression model if preliminary inspection of the data indicate that the time development during treatment has a different slope than during the follow-up period. If the time-development is better represented by a continuous equation (e.g., time, or SQRT (time), or log (time)) than we will do sensitivity tests of the treatment x time interaction for the treatment period, in addition to the test for the whole assessment period. We will also examine the between group differences at specific time-points, e.g., at the end of treatment and the final follow-up. For categorical outcome variables, counts appropriate forms of mixed regression will be chosen, with attention to non-normal residuals (negative binomial, Poisson, and gamma, etc.). Mixed regression methods will also be used to identify predictors/moderators that are related to treatment outcomes. Survival analysis will be used to analyze treatment retention.

### Cost-effectiveness study

#### Assessing resource consumption and productivity loss

Costs are assessed from several societal perspectives, including direct medical, direct non-medical and indirect costs, through structured face-to-face interviews (“Cost Interview”). The Cost Interview was used in another German study [10, 30] that examined the cost of BPD. Prior to the current study, modifications were made to improve clearness/comprehensibility, and additional items were incorporated into the Cost Interview. Items that are related to direct resource consumption include psychiatric and general hospital days, days in a psychiatric day clinic and assisted living programs, drug intake, visits to emergency rooms, outpatient psychotherapists, psychiatrists, general practitioners, medical specialists, occupational therapists, physical therapists, community based counselors and crisis centers. Items that are related to non-medical resource consumption include informal care, which occurs when significant others take over domestic tasks without payment. Also, we assess incidents of deviant behavior (e.g., traffic offenses, bodily harm) and their associated consequences, such as police operations or monetary compensation for damages. Productivity loss is captured with questions on employment status, the source of income, gross income, the number of weeks of employment, unemployment and work disability since the last assessment. Employed patients are asked about their average weekly work hours and the number of days that they were absent from work.

Resource consumption and productivity loss is retrospectively assessed. The baseline assessment occurs at the time of inclusion in the study and reflects the previous 12 months. During treatment and the 6 and 12-months follow-up, the Cost-Interview is conducted every six months. Further, the cost-interview is performed at 24 month follow-up about the previous 12 months (see Table 2). Wagner et al. found that it was difficult to clearly distinguish between BPD-related costs and costs due to other mental disorders because some symptoms (e.g., binge eating) are both a diagnostic criterion of BPD and other mental illnesses [10, 30]. Hence, the current study distinguishes between the costs that are due to psychological disorders and somatic diseases. First, the Cost-Interview is sent to patients for self-evaluation and to prepare for the interview appointment. In the interview appointment, missing items are assessed and it is determined whether resource consumption and productivity loss were due to psychological disorders or medical diseases.

#### Cost calculation and efficiency analysis

Costs are expressed in Euros using the 2015 price level. To calculate direct costs, we multiply resources by their corresponding unit cost (i.e., the cost of a particular medical or non-medical treatment). In contrast to other countries, such as Great Britain, there is no obligatory unit cost list in Germany. In the current study, unit costs are calculated based on Bock et al.’s [96] recent proposals. Bock et al. provided unit costs from a societal perspective for resources, including inpatient and outpatient medical care. Additionally, the authors showed how to update those unit costs on a yearly basis using regularly published sources. Indirect Costs are calculated according to the Human Capital Approach. Compared to the Friction Cost method, the Human Capital Approach is more applicable to BPD patients [97] because a sizable proportion of BPD patients are work disabled and work disability is not counted in the Friction Cost Method. We count productivity loss due to absences from paid work and productivity losses due to work disability. For patients with a paid job, we multiply the days absent from work by individual labor costs. Work disability-related costs are calculated based on the assumption that patients without BPD would pursue a paid job. Therefore, we multiply the national average monthly labor costs by the number of months that the patients were work-disabled.

The economic analysis is also based on the intention-to-treat principle. To determine the efficiency of DBT and ST, we will perform cost-effectiveness and cost-utility analyses. We will calculate two incremental cost-effectiveness ratios (ICER; the difference in costs between the two interventions divided by their difference in effectiveness). In the context of the cost-effectiveness analysis, we will calculate the costs per 10 BPDSI improvement points. For the cost-utility analysis, the costs per quality adjusted live years (QALY) will be calculated based on the EQ-5D questionnaire.

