In sum, there are promising findings on the clinical efficacy and effectiveness of DBT and ST in treating BPD [20]. Moreover, both treatments lead to impressive reductions in direct and indirect health care costs (approx. 10,000 € per patient per year) [30, 51]. However, research has not yet compared these two methods. A treatment comparison would be interesting for psychotherapy research because both treatments have different approaches to treating BPD and focus on different techniques, despite several common factors (see also methods and a detailed overview in [55]).

The objective of this study is to compare the (cost)-effectiveness of DBT and ST in patients who have BPD. The PRO*BPD trial is the first randomized trial to compare these two methods. The primary hypothesis is that DBT and ST significantly differ in reducing BPD-severity (two-sided hypothesis). A two-sided hypothesis was chosen because information from literature does not allow predictions on the directionality of the difference (see discussion for more information on this theme).

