In addition, we evaluate the costs and perform an economic evaluation from a societal perspective. Thus, a secondary hypothesis is that the two methods differ in their cost-effectiveness. In a budget-constrained health care system, there is an urgent need for detailed information on the costs and benefits of an intervention to inform decisions on resource allocation. A major challenge for BPD-specific psychotherapy is to demonstrate that the treatment leads above and beyond reductions in external BPD-symptoms (e.g., self-harm, suicide attempts or impulsive behavior) also to improvements in internal BPD-symptoms (e.g., chronic dysphoria, loneliness or feeling empty), as well as associated difficulties, including global psychosocial functioning, comorbid disorders, and quality of life. Thus, the outcomes of this study address not only BPD-symptoms but also the quality of life, psychosocial function and participation, general psychopathology and other psychiatric disorders. Further secondary hypotheses involve different effects of the two treatments in the different BPD symptoms and other secondary outcomes. Also, there might be different effects in subgroups of patients with BPD (e.g., different effects based on comorbid disorders or patterns of BPD symptoms) which will help to advance our knowledge about which treatment should be offered to which patient. More support from literature and discussion of the secondary hypotheses can be found in the discussion section.

We study moderating and mediating variables (e.g., sex, age, the severity of BPD-symptoms, comorbidity, traumatic experiences during childhood, experiential avoidance) through exploratory data analysis. Furthermore, we conduct a qualitative study on patients’ experiences with the two treatment methods.

The PRO*BPD study is conducted in the routine clinical setting of an outpatient clinic and responds to the call for ‘real world’-studies. As such, we use minimal exclusion criteria, set low barriers to patient participation and guarantee the clinical equipoise of the two treatment programs. Thus, we include BPD patients with the entire range of mental disorder comorbidity and high BPD severity and minimize resistance for participating in a clinical trial with randomization.

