#### Sample size

The primary variable for calculating the sample size is the BPDSI total score. The sample size calculation is based on the number of participants that are needed to detect a clinically significant difference between the two conditions. Although the meta-analyses on DBT demonstrated global changes in effect sizes (ES) of d = 0.5 [27] and ST had a higher change in ES for borderline-specific symptoms (d = 2,96 [45] and d = 2.81 [44]), these cannot reliably be compared because they reflect different samples and outcome instruments, and there has been no direct comparison between the two methods. Therefore, we chose a medium ES of d = 0.5 for detecting group differences for the sample size calculation. Detecting a difference with this ES could strongly influence clinical decision making. As such, *n* = 64 patients per condition are required to detect group differences with a Type I error of 5% and a power of 80% (Type II error = 20%). Assuming an attrition rate of 20%, we will recruit *n* = 160 patients.

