## Discussion

This article described the study design of the PRO*BPD trial, which is a randomized trial that compares the clinical and cost effectiveness of DBT and ST for treating BPD offered in a 1.5-year outpatient treatment program. To the best of our knowledge, this is the first study that compares ST and DBT. Because these two methods are the primary CBT treatments for BPD, this comparison is long overdue. The primary hypothesis is that the two psychotherapeutic methods significantly differ in reducing BPD-severity (two-sided hypothesis). A two-sided hypothesis was chosen, because DBT and ST have never been directly compared before. Further, trials investigating the clinical effectiveness of one of the two methods are not comparable, as they used different outcome variables (DBT trials mainly focusing on suicidality, self-injuring and impulsive behaviors, while ST trials focusing on all nine BPD-criteria). Also, different samples of patients and doses of treatment have been investigated (for DBT mainly one year outpatient treatment, while ST mainly has been offered more extended treatment periods). Given these differences there is considerable uncertainty about which treatment is superior in reduction of overall BPD-severity.

A major criticism of the PRO*BPD trial might be, that we compare two bona fide psychotherapies and in line with the so-called ‘Do-do-bird-verdict’ according to the meta-analysis of Wampold et al. [100], a probable result might be, that there is no difference in the primary outcome between the two conditions. However, there is meta-analytic empirical evidence that casts doubt about a ‘Do-do-bird-verdict’ on psychotherapies for (B)PD. For instance, Wampold’s group has published a meta-analysis indicating that specific evidence-based psychotherapies do better than treatment-as-usual, and that some specialized psychotherapies do better than others [101]. Similarly, a meta-analysis demonstrated that specialized psychotherapies for BPD (the so-called ‘big-four’) do significantly better than control treatments [102]. Thus, the position that all treatments are equal in effectivity (and dropout), is not unequivocally supported by the data. Moreover, it is the present authors’ view that the question to what degree DBT and ST are similar in effectiveness and dropout rates from treatment, is an empirical issue which cannot be solved by a priori beliefs.

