Another point to consider is that the therapist teams have high enthusiasm and allegiance to the two methods and receive intensive supervision and training. On the one hand, this guarantees that the two methods are provided in the way they are supposed to be (‘adherence’). In contrast, one could argue that the time factor of training and weekly supervision is difficult to embed in general clinical practice, which may endanger the ‘real world’ character of the study. However, training and supervision are essential parts of both treatment programs and if this is necessary for successful treatment, training and supervision should be implemented everywhere in general clinical practice. Cost-effectiveness analyses will demonstrate whether this ‘extra time’ is cost-effective.

Another crucial issue is the treatment dose, as DBT and ST are applied with very heterogeneous doses and durations. In most DBT studies, the treatment duration was one year with one individual (60 min) and one long group session (180 min) per week. However, some studies tested shorter treatments, e.g., six months. In contrast, ST studies that examined individual ST for BPD had a treatment duration of 1.5 years or more with up to two weekly individual sessions. The one trial that tested group ST treatment offered only eight months of treatment with one weekly group session, but patients continued with individual TAU. We decided to provide the same treatment doses and durations for both conditions to better control for non-specific factors. For this trial, we identified a format that is feasible in the German health care system and is not too short to increase benefits for severely impaired patients. From our experience, one year of therapy is usually not adequate for these patients. Thus, we decided for a treatment duration of 18 months, with weekly individual and group sessions. This should suffice for applying the full range of ST and DBT treatment techniques without excessive redundancy.

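### The comparison of two trained and supervised arms cannot show whether training and supervision pay, and the ICER, the only statistic named for the cost-effectiveness hypothesis, is unstable when effects are close

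*Protocol article*

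**What the plan says.** The Background states that "a secondary hypothesis is that the two methods differ in their cost-effectiveness". The section on cost calculation and efficiency analysis announces cost-effectiveness and cost-utility analyses by intention to treat, and then names the statistic: "We will calculate two incremental cost-effectiveness ratios (ICER; the difference in costs between the two interventions divided by their difference in effectiveness". One ratio is per 10 points of BPDSI improvement, the other per QALY from the EQ-5D. The article names no other statistic for the economic comparison.

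The Discussion takes up the objection that training and weekly supervision are hard to fit into ordinary practice. It closes the paragraph with "Cost-effectiveness analyses will demonstrate whether this" additional time is cost-effective.

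Three other places bear on this. The section on therapists, training and supervision provides training and weekly supervision in both therapies. The Design section and the limitations in the Discussion give two active arms and no untreated or usual-care control. The limitations also concede that differences smaller than the planned medium effect are possible between two established psychotherapies and might be missed.

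**The concern.** **Training and supervision.** To learn whether an input is worth its cost, one needs patients treated with it and patients treated without it, or with less of it by design. This trial randomises between two therapies that both have it. If the sentence stands, readers may take any favourable economic result as evidence that the training and supervision paid for themselves. The trial would contain no evidence for that.

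**The ratio.** An ICER does not carry its own meaning. Cheaper and better gives a negative ratio, and so does dearer and worse. When the effect difference is near zero, the ratio swings between large positive and large negative values. Its confidence interval is a bounded range only if the effect difference itself is significantly different from zero. The article states a hypothesis of a difference in cost-effectiveness, names only this statistic, and concedes the situation in which the statistic works badly. At stake is whether the secondary hypothesis gets an interpretable answer when the two therapies turn out close.

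**Working it through.** **Training and supervision: the statements side by side.**
- Claim (Discussion): the economic analyses will settle whether the extra time is cost-effective.
- Estimand (cost calculation section): difference in costs between the two interventions over their difference in effect, that is, DBT against ST.
- Delivery (section on therapists, training and supervision): training and weekly supervision in both arms.
- Comparators (Design; Discussion): two active arms only.

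Whatever training and supervision contribute is present on both sides of the contrast. At most, a difference between the arms in how much is delivered enters the cost difference, mixed with every other difference between the therapies. No analysis of these two arms yields a comparison of with against without.

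**The ratio: inputs.**
- Hypothesis: "The primary hypothesis is that DBT and ST significantly differ in reducing BPD-severity (two-sided hypothesis".
- Effect size: "Therefore, we chose a medium ES of d = 0.5 for detecting group differences for the sample size calculation".
- Error rates: 64 "patients per condition are required to detect group differences with a Type I error of 5% and a power of 80" per cent.
- Attrition: "Assuming an attrition rate of 20%, we will recruit" 160 patients, allocated 1:1.

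**Reproducing the plan's figure.** The normal approximation gives n = 2 × (1.96 + 0.84)² / 0.5² ≈ 63 per arm. The two-sample t-test gives 63.77, hence 64. With 20% attrition, 64 / 0.8 = 80 per arm, or 160 in total. Power at 64 per arm is 0.801. The stated sample size is correct and is not in dispute.

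**How often the ratio's interval is unbounded.** On the standardised scale, SE = sqrt(2/n): 0.177 at 64 per arm and 0.158 at 80. A 95% Fieller interval for a ratio is bounded only when the denominator differs from zero at the two-sided 5% level. So

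P(unbounded) = P(|d-hat| < 1.96 × SE), and P(wrong-sign denominator) = Φ(−d/SE).

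For d = 0.25 at 64 per arm, d/SE = 0.25/0.177 = 1.41, and Φ(1.96 − 1.41) − Φ(−1.96 − 1.41) ≈ 0.71. The wrong-sign probability is Φ(−1.41) ≈ 8%.

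Results at 64 per arm:
- d = 0: unbounded in 95%; the sign is a coin toss
- d = 0.1: unbounded in 91%; wrong sign in 29%
- d = 0.2: unbounded in 80%; wrong sign in 13%
- d = 0.25: unbounded in 71%; wrong sign in 8%
- d = 0.3: unbounded in 61%; wrong sign in 4.5%
- d = 0.5: unbounded in 19% (normal) or 20% (t-test); wrong sign in 0.2%

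At 80 per arm the unbounded share is 90% at d = 0.1, 76% at d = 0.2, 53% at d = 0.3 and 12% at d = 0.5.

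These results need only n and d, and changing the unit to 10 BPDSI points does not alter them. They cover the BPDSI ratio only. The article gives no expected QALY difference or SD, so nothing comparable can be computed for the cost-utility ratio.

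**The alternative on the same data.** Incremental net benefit is λ × (effect difference) − (cost difference), where λ is the amount that a decision maker would pay per unit of effect. It has no denominator. The documents give no cost SD, cost–effect correlation or threshold, so three values are assumed for illustration: a cost difference of 0.5 SD, zero correlation, and λ of one cost SD per effect SD. In one million simulated trials per setting at 64 per arm:
- ICER at d = 0.2: central 95% sampling range about −21.8 to 25.5 around a true value of 2.5.
- ICER at d = 0.5: about 0.27 to 3.41 around a true value of 1.0.
- Net benefit: 95% coverage of 0.950 at each d tried (0, 0.1, 0.2 and 0.5), and type I error of 0.050 when the true net benefit is zero. The half-width is constant: 1.96 × 0.177 × sqrt(2) = 0.49 SD (0.44 SD at 80 per arm).

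**The case against.** **The article does not exclude other methods.** It does not say that ICERs are the only output, nor does it label them a test. Bootstrap intervals, thresholds and acceptability curves are commonly left to an analysis plan, and that plan is not shown. This stands: their absence is not the finding. What remains is narrower. The article does name a statistic alongside its hypothesis, and that statistic is a poor choice in a situation the article concedes.

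**The hypothesis remains testable.** A reader might infer that the trial cannot test its cost-effectiveness hypothesis. The documents do not support that. Costs, BPDSI and EQ-5D are collected for each patient in both arms, and a valid test can be built from them. The sign ambiguity also disappears once the cost and effect differences are shown separately.

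**The authors do not forecast a null result.** The remark that "a probable result might be, that there is no difference in the primary outcome between the two conditions" could be read that way. It describes a criticism that the authors go on to rebut. The fair source is their limitations paragraph, which concedes only that smaller effects are possible.

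**The percentages restate the power calculation.** At d = 0 the figure is one minus alpha, and at d = 0.5 it is the stated type II error. This is true, and it is why the result needs no outside input. The intermediate values show how quickly the ratio deteriorates. More than 64 per arm may be analysed, which is why figures for 80 are given too.

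**Programme hours may be costed elsewhere.** A reader might infer that training, supervision and telephone time are left out, because the listed items of the Cost Interview do not include them. That list describes an interview with patients, and the Design section refers separately to assessing treatment costs. The article does not show that these costs are excluded. The argument on training and supervision rests on the missing comparator and does not need this.

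**Conclusion.** The sentence on training and supervision announces a conclusion that the design cannot give. This holds in full, and no unseen analysis plan could repair it, because the comparator does not exist. It is one sentence in the Discussion and is attached to no stated hypothesis.

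The point on the ratio holds in a limited form: the only statistic named for a stated hypothesis behaves badly if the therapies are close. Its size is an unbounded 95% interval for the BPDSI ratio in about 71% of trials at d = 0.25 and 19–20% at d = 0.5 with 64 per arm, falling to 12% at d = 0.5 with 80. These figures assume a simple two-group comparison with the precision used in the sample size calculation; a repeated-measures model could be more or less precise. The net-benefit illustration also rests on the assumed cost inputs and on normal sampling. Real costs are usually skewed, hence the bootstrap in the fix. The weakness is in the statistic and not in the data collected.

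**What to change.** 1. In the Discussion, delete the sentence on the cost-effectiveness of the extra time, or limit it to the relative cost-effectiveness of DBT and ST as delivered, training and supervision included. This costs one sentence.

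2. In the section on cost calculation and efficiency analysis, make incremental net benefit the test of the cost-effectiveness hypothesis. State in advance a range of thresholds per 10 BPDSI points and per QALY. Obtain intervals by a bootstrap that resamples each patient's costs and effects together. Keep both ICERs as descriptive figures, reported next to the separate cost and effect differences. If the analysis plan already does this, a cross-reference is enough. The cost is a few lines of analysis text and agreement on the thresholds; no new patient data are needed.

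Separate costing of training, supervision or telephone hours from clinic records is not asked for. The documents show neither that such costs are excluded nor that such records exist.
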